### Statistical methods

A detailed statistical plan, including data requirements and processing methods, will be provided to the statisticians by the research team before data analysis. Statisticians, independent and blinded to the test settings, will execute the analysis as per this plan.

### Behavioral analysis

Data analysis will be conducted by an independent statistician using SPSS version 26.0 (SPSS Inc., Chicago, IL, United States). Two-tailed analyzes will be performed, with statistical significance set at *p* < 0.05.

Intention-to-treat analyzes will be applied wherever possible, complemented by subgroup and sensitivity analyzes to identify potential heterogeneity in results. Continuous variables will be expressed as means ± standard deviations, while categorical variables will be presented as numbers and percentages. The normality of continuous variables will be assessed using the Kolmogorov–Smirnov test. For normally distributed data, within-group differences will be evaluated using paired-sample t-tests, and between-group analyzes will employ Analysis of Variance (ANOVA) and the Kruskal–Wallis test. Non-parametric tests will be used for data with skewed distributions.

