### Objective

(1) To evaluate the effects of Baduanjin exercises on emotion control, attention, and cognitive abilities compared to regular aerobic exercise and a control group on a waiting list.(2) To visually demonstrate the impact of Baduanjin exercises on brain function related to emotion regulation and its influence on associated networks, including attention, cognitive abilities, motor skills, and sensory functions.

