### Participants

The trial aims to recruit 99 participants from the School of Acupuncture and Tuina at Chengdu University of Traditional Chinese Medicine. Recruitment will be facilitated through various channels, including campus radio broadcasts, on-campus advertising, and online platforms.

They will be randomly assigned in a 1:1:1 ratio to the Baduanjin group, the aerobic exercise group, or the waiting-list group.

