### Procedure

The study’s physical and psychological outcomes will be evaluated at three key intervals: one week before the intervention, at 12 weeks (mid-intervention), and at 24 weeks (post-intervention). Additionally, 20 individuals from each group will be selected randomly for pre-and post-intervention fMRI scanning. The study’s process and timeline are depicted in Figure 1 and Table 1.

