**Figure 1 fig1:**
[figure not shown]
The roadmap of the study process.

**Table 1 tab1:** Schedule of the trial.

Items			Study process			
			Baseline period	Intervention period (0-24 week)		
Time point			1-week	0-week	12-week	24-week
*Screening and preparation*						
Informed consent			√			
Randomization and allocation			√			
Coaching seminar			√			
*Intervention*						
Baduanjin group				√	√	√
Aerobic exercise group				√	√	√
Waiting group				√	√	√
*Clinical outcomes measurement*	*Primary outcomes*	*Emotional control*				
		SPQ	√		√	√
		IRI	√		√	√
		POMS	√		√	√
		CD-RISC-25	√		√	√
		ECS	√		√	√
		*Attention control*				
		Schulte table software	√		√	√
		*Cognitive function*				
		CFS	√		√	√
	*Secondary outcomes*	*Hand motor function*				
		Hand grip strength	√		√	√
		Finger pinch strength	√		√	√
		Purdue pegboard	√		√	√
		*Hand sensory*				
		Touch-Test	√		√	√
		Two-Point test	√		√	√
		Acupuncture test	√		√	√
*Image scanning*						
fMRI			√			√
*Subject safety*						
Laboratory examination			√			
AEs				√	√	√

This study includes a 1-week advance baseline period and a 24-week intervention period for each participant.

SPQ, the Situational Pain Questionnaire; IRI, the Interpersonal Reactivity Index; POMS, the profile of Mood States; CD-RISC-25, the Chinese version of the Connor-Davidson Mental Toughness Scale; ECS, the Emotional Contagion Scale; CFS, the Cognitive Flexibility Scale; AEs, Adverse events. Laboratory test: including routine examination of blood, urine, and stool, blood biochemical test (including liver and kidney function), and electrocardiogram examination.

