### Primary outcome measurement

Primary outcomes focus on attention control, cognitive function, and emotional control, assessed using various tools:

Schulte Table Software (Prokopenko et al., 2013) for evaluating concentration and attention switching.Cognitive Flexibility Scale (CFS) (López et al., 2022) for assessing cognitive flexibility.To evaluate the capacity for regulating emotions: Emotional Contagion Scale (ECS) (Doherty, 1997) for measuring susceptibility to others’ emotions.

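### One p < 0.05 threshold and an omnibus three-arm test cover at least three primary outcomes at two visits, with no primary visit, contrast or success rule

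*Protocol article*

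**What the plan says.** All of this is in the protocol article.

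- **Decision rule** (Behavioral analysis): "Two-tailed analyzes will be performed, with statistical significance set at *p* < 0.05". Between-group comparisons use ANOVA and Kruskal–Wallis, and within-group changes use paired t-tests. No pairwise procedure, gate or adjustment is named.
- **Primary outcomes** (Primary outcome measurement): "Primary outcomes focus on attention control, cognitive function, and emotional control, assessed using various tools". One instrument is listed per domain: Schulte table, Cognitive Flexibility Scale and Emotional Contagion Scale. Three is a minimum count, because the Schulte table is used "for evaluating concentration and attention switching", which could give two scores. Table 1 lists seven instruments under "Primary outcomes". That conflict is a separate matter, and the count here is three.
- **Visits** (Procedure): outcomes are assessed "one week before the intervention, at 12 weeks (mid-intervention), and at 24 weeks (post-intervention"). Neither post-baseline visit is called primary.
- **Arms** (Participants): "They will be randomly assigned in a 1:1:1 ratio to the Baduanjin group, the aerobic exercise group, or the waiting-list group".
- **Question** (Objective 1): Baduanjin is to be judged "compared to regular aerobic exercise and a control group on a waiting list", which makes two specific contrasts.

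**The concern.** There are two problems.

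First, a 5% level per test is not a 5% level for the primary claim when several primary tests are run and the article does not say which of them decides. The visit, outcome and contrast that carry the claim could be chosen once results are known, and the stated level would then understate the chance of a false positive.

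Second, the named test does not match the question. A three-arm omnibus test asks whether any of the three means differ. Objective 1 asks whether Baduanjin differs from each of two comparators. If aerobic exercise works and Baduanjin does nothing, the omnibus test can still be significant, and that result says nothing in favour of Baduanjin. This mismatch would exist even with one outcome and one visit.

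**Working it through.** **The plan's own figure.** The only stated figure is the 0.05 level. The article gives no familywise error rate, so there is none to reproduce.

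**Inputs from the article.** Level 0.05 two-sided; K = 3 primary outcomes; V = 2 post-baseline visits; 3 arms; 33 enrolled per arm with 10% dropout, so 33 × 0.9 = 29.7, taken as 30 analysed per arm.

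**Assumptions (not in the article).** Normal outcomes; correlation 0 to 0.5 between outcomes and 0 to 0.7 between visits.

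**Step 1: omnibus tests, independence.** The chance of at least one false positive among k tests is 1 − 0.95^k.

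- Week 24 only, k = 3: 1 − 0.95^3 = 14.3%.
- Both visits, k = 3 × 2 = 6: 1 − 0.95^6 = 26.5%.

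**Step 2: with correlation.** Simulation under the global null, 30 per arm, 10,000 trials per setting, range over the correlation grid, three primary outcomes:

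| Tests counted | Week 24 only | Both visits |
|---|---|---|
| Omnibus ANOVA | 12–14% | 21–27% |
| Two Baduanjin contrasts, ungated | 22–25% | 35–44% |
| All three pairs, ungated | not tabulated | 44–55% |

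The two lower rows need pairwise tests run regardless of the omnibus result. If a Baduanjin contrast is read only after a significant omnibus test, the rate is lower. With correlation 0.3 between outcomes and 0.6 between visits, it is about 11–12% at week 24 and about 20% over both visits.

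**Step 3: the success rule.** The figures above assume that one significant primary outcome is enough. If all three must be significant at one named visit, a false claim requires every test to pass, including at least one true null tested at 0.05. The error for that claim is then at most 5%.

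**Step 4: omnibus test against Objective 1.** Suppose Baduanjin equals waiting list and aerobic exercise is shifted by 0.74 SD (an assumption). With 30 per arm, the noncentrality is 30 × 0.74² × 2/3 = 10.95 on 2 and 87 degrees of freedom, and the ANOVA is significant in about 84% of trials. None of those results reflects a Baduanjin benefit.

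**Step 5: what the fix controls.** Within one outcome, two contrasts in fixed order at 0.05/3 have a familywise error of at most 0.05/3. Over three outcomes the total is at most 3 × 0.05/3 = 5%. Under independence it is 1 − (1 − 0.0167)^3 = 4.9%.

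**The case against.** The strongest reply is that a condensed article need not carry multiplicity detail. It announces a detailed statistical plan to be supplied before analysis, and that plan may name the visit, the contrasts and an adjustment. The trial also describes itself as preliminary and exploratory, and its limitations section calls for larger multi-center trials. Week 12 is labelled mid-intervention and imaging is only pre and post, so week 24 is the natural primary visit.

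Much of this stands, and it lowers the severity. It does not remove the point, because the article itself fixes the level, the between-group test and several primary outcomes, and these do not fit together or fit Objective 1. The article also states a directional hypothesis and says that its findings will provide empirical support for using Qigong to improve acupuncturists' skills.

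Two stronger readings are tempting.

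- A reader might infer that any single significant result counts as support for H1. The article states no such rule. H1 lists emotion regulation, attention and cognition together, which can equally be read as requiring all three. The text leaves this open.
- A reader might infer that the false-positive rate is close to one half. That needs ungated pairwise tests at both visits, and the article names no pairwise tests. Pairwise tests gated by the omnibus result cannot exceed the omnibus rate under the global null.

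**Conclusion.** The concern holds in a limited form. As written, the article sets a per-test level with no rule that turns it into a level for the primary claim, and it names a between-group test that does not isolate the Baduanjin comparisons.

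If any one outcome suffices, the chance of a false significant primary omnibus test is about 14% at week 24 alone (12–14% over the assumed correlations) and about 21–27% if both visits count. It is about 35–55% only with ungated pairwise tests at both visits. It is not inflated if all three outcomes must succeed at one named visit. All figures assume about 30 analysed per arm.

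Severity: should be fixed. A reader might take this as a defect that invalidates the trial, but the stated preliminary and exploratory purpose does not support that, and the later statistical plan could still settle it.

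**What to change.** Write the following into the protocol or the statistical plan before any outcome data are seen.

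1. Name week 24 as the primary time point.
2. For each of the three outcomes in the Primary outcome measurement section, test Baduanjin against waiting list. Only if that is significant, test Baduanjin against aerobic exercise. Use a fixed 0.05/3 = 0.0167 for both tests.
3. Do not pass alpha from one outcome to another. A Holm step-down across outcomes, with the second contrast tested at whatever level its outcome reached, spends alpha twice. If Baduanjin equals aerobic exercise and both clearly beat waiting list, the familywise error with independent outcomes is 1 − (1 − 0.0167)(1 − 0.025)(1 − 0.05) = 8.9%. In the same situation the fixed 0.05/3 rule stays below 5%.
4. Alternatively, state that all three outcomes must succeed, each at 0.05, at week 24.
5. Report week 12, secondary and aerobic versus waiting-list results as estimates with 95% confidence intervals and no significance claim.

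The cost is wording and some sensitivity, with no extra participants. At an assumed 30 per arm and 80% power, the detectable standardized difference for one contrast rises from about 0.74 at 0.05 to about 0.86 at 0.05/3. The all-must-succeed option keeps 0.74 per outcome but lowers joint power: with 80% power for each of three independent outcomes, 0.8^3 = 51%.

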### Hypotheses

Acupuncturist Long-term participation in Qigong will differ significantly from aerobic and waiting exercises in terms of emotional cognition and attention.

*H1*: Long-term participation in Qigong, specifically Baduanjin, is expected to markedly improve acupuncturists’ capabilities in emotion regulation, attention, and cognition.

*H2*: It is also anticipated to cause observable changes in the structure and functional dynamics of specific brain regions.

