#### Sample size estimation

This preliminary exploratory clinical randomized controlled neuroimaging trial is informed by similar studies and the minimal sample size guidelines for clinical investigations (Yuen et al., 2021). Accounting for a potential 10% dropout rate, we aim to enroll 33 subjects per group, totaling 99 subjects across three groups. A previous neuroimaging study (Szucs and Ioannidis, 2020) indicates that an imaging sample size of more than 15 per group yields reliable and consistent results. Therefore, 20 subjects from each group will be randomly selected for functional magnetic resonance imaging (fMRI) scans.

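### The between-group tests name no baseline adjustment, and within-group paired t-tests stand beside them with no statement that the between-group test decides the hypothesis

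*Protocol article*

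**What the plan says.** Under Behavioral analysis, the protocol article names the tests for the behavioural outcomes. For normally distributed data, "within-group differences will be evaluated using paired-sample t-tests, and between-group analyzes will employ Analysis of Variance (ANOVA) and the Kruskal–Wallis test". Skewed data go to non-parametric tests, and the choice follows a distributional check: "The normality of continuous variables will be assessed using the Kolmogorov–Smirnov test". All tests are two-sided at 0.05. The same section adds that "Intention-to-treat analyzes will be applied wherever possible".

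No baseline covariate, repeated-measures term or group-by-time term is named. The response variable of the ANOVA (follow-up score or change from baseline) is not given. Procedure and Table 1 place every behavioural outcome at one week before the intervention, week 12 and week 24.

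Objective 1 and the opening sentence of Hypotheses set Baduanjin against both aerobic exercise and the waiting list. H1 is worded differently: Baduanjin practice "is expected to markedly improve acupuncturists’ capabilities in emotion regulation, attention, and cognition", with no comparator. On size, Sample size estimation says: "Accounting for a potential 10% dropout rate, we aim to enroll 33 subjects per group, totaling 99 subjects across three groups". It gives no effect size, SD or power. Statistical methods announces a more detailed plan for the statisticians, which is not shown.

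**The concern.** Two features of the stated method fit the design poorly.

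First, the between-group comparison is the trial's question, and the tests named for it include no adjustment for a baseline that is collected on everyone. With about 30 completers per arm and no stated power target, there is little precision to spare.

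Second, the paired t-tests are listed beside the between-group tests, at the same significance level, and neither is ranked above the other. A before–after test in one arm contains no comparator. The Schulte table, a primary outcome, is a performance task given three times, and the pegboard and needling tests are repeated in the same way, so gains from practice in all arms are plausible. Because H1 speaks only of improvement, a significant paired test in the Baduanjin arm could be taken to confirm it. The familiar mistake would follow: significant in Baduanjin, not significant in control, therefore effective.

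**Working it through.** **Inputs from the protocol article.** 33 per arm, 1:1:1 allocation, 10% dropout, two-sided 0.05. Completers per arm: 33 × 0.9 = 29.7, taken as n = 30. The figure of 33 cannot be reproduced from an effect size, because none is stated.

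**Assumptions (not in the document).** Standardised difference d = 0.5. Correlation between baseline and follow-up score r = 0.5, 0.6 or 0.7. Equal SDs of 1 at both times.

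**Power of one between-arm contrast.** Two-sample t-test, 58 degrees of freedom, critical value 2.002, noncentrality = (d / s) × √(n/2) = (0.5 / s) × √15 = 1.936 / s. The SD s depends on the response variable:

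- follow-up score: s = 1
- change from baseline: s = √(2(1 − r))
- baseline-adjusted: s = √(1 − r²)

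| r | s, change | s, adjusted | Power, follow-up score | Power, change | Power, adjusted |
|---|---|---|---|---|---|
| 0.5 | 1.000 | 0.866 | 48% | 48% | 59% |
| 0.6 | 0.894 | 0.800 | 48% | 57% | 66% |
| 0.7 | 0.775 | 0.714 | 48% | 69% | 76% |

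The one degree of freedom spent on the covariate does not change these figures at the precision shown. At r = 0.3 the powers are 48% (follow-up), 36% (change) and 51% (adjusted). Adjustment is the best of the three at every r tried. Change scores are worse than follow-up scores when r is below 0.5.

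In terms of variance, adjustment removes r²: 25%, 36% and 49% at r = 0.5, 0.6 and 0.7. Against a follow-up-score analysis this equals 1/(1 − r²) − 1 = 33%, 56% and 96% more participants.

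**Paired test when the arms do not differ.** Assume every arm gains g = 0.4 SD with r = 0.6.

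- SD of change: √(2 × 0.4) = 0.894.
- Noncentrality: (0.4 / 0.894) × √30 = 2.449, with 29 degrees of freedom and critical value 2.045.
- Probability that the Baduanjin paired test is significant: 0.658.
- Probability that Baduanjin is significant and the waiting list is not: 0.658 × (1 − 0.658) = 0.225, about 22%.

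Over g = 0.2 to 0.5 and r = 0.5 to 0.7, the first probability runs from 18% to 93% and the second from 7% to 25%.

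**Between-group ANOVA in the same situation.** In 20,000 simulated trials (g = 0.4, r = 0.6, 30 per arm, no group difference), a one-way ANOVA on follow-up scores rejected in 4.7%, in line with its nominal 5%. A shared practice effect therefore does not disturb the randomised comparison.

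**The case against.** The strongest reply is that the text is less committed than a critical reader might suppose, and much of that reply stands.

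- A reader might infer that the baseline is ignored. The article does not say so. The ANOVA response is unstated, and an ANOVA of change would use the baseline, though less efficiently than adjustment. Nor is the named method the least efficient available, since at low r change scores do worse than follow-up scores.
- A reader might infer that the paired tests are the planned evidence of effect. They are only listed. Objective 1 and the opening hypothesis are comparative, and only H1 is worded without a comparator.
- A reader might infer that practice can pass as a Baduanjin effect in the planned comparison. It cannot: the arms are randomised, share one assessment schedule, and the ANOVA holds its level.
- A reader might infer that the intention-to-treat statement cannot be met because these tests drop anyone missing a visit. The statement is qualified, sensitivity analyses are mentioned, and imputation is not ruled out.
- Naming Kruskal–Wallis in the sentence on normal data may be loose drafting, since the next sentence assigns non-parametric tests to skewed data.

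The article also calls the trial preliminary and exploratory, and a fuller plan is announced. That does not remove the point. The article goes beyond leaving the method open: it names the tests, and nothing says that the later plan will replace them.

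**Conclusion.** The point holds as a matter of efficiency and interpretation; the planned between-arm comparison itself is valid. Relative to the best use of the same data, the shortfall at d = 0.5 is 12, 18 and 28 percentage points of power at r = 0.5, 0.6 and 0.7 if the ANOVA uses follow-up scores (rounded from unrounded powers). It is about 12, 10 and 7 points if the ANOVA uses change scores. Adjustment is better under either reading. The paired tests can show a significant Baduanjin change in about two trials in three with no group difference, under the assumed shared gain of 0.4 SD and r = 0.6, but this misleads only if they are treated as evidence of effect. All these sizes rest on assumed d, r and practice gain, which the article does not give. Since the comparison keeps its error rate and the trial is described as exploratory, this is a change that should be made, not one on which the trial's validity depends.

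**What to change.** In Behavioral analysis, name one primary between-arm model for each continuous outcome. It can be an ANCOVA of the week-24 score with the baseline score as covariate, or a mixed model over weeks 12 and 24 with arm, visit, arm-by-visit and baseline score. The mixed model also keeps anyone with at least one follow-up visit, which serves the intention-to-treat aim. Report the adjusted Baduanjin minus waiting-list and Baduanjin minus aerobic differences with 95% confidence intervals.

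State that this between-arm test decides H1, and label within-arm paired changes as descriptive. Use Kruskal–Wallis or another rank-based test only as a sensitivity analysis, not as an alternative selected by a normality test, so that each hypothesis has one primary p-value.

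The cost is analysis wording only. The models use data already scheduled for collection and can be run in the SPSS version the article names. The change should be made before unblinded analysis.

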#### Inclusion criteria

Subjects will be recruited if they:

Be aged between 18 and 25 years;Be right-handed;Provide informed consent;Be a full-time acupuncture student with completed courses in acupuncture and moxibustion (45 h), meridians and acupoints (84 h), and possess clinical practice experience, as evidenced by passing semester examinations.

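### Within-arm paired t-tests share the p < 0.05 status of the between-arm tests, and H1 names no comparator, so a pre-post change could be read as a Baduanjin effect

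*Protocol article*

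**What the plan says.** The Behavioral analysis section of the protocol article sets one rule for all behavioural tests: "Two-tailed analyzes will be performed, with statistical significance set at" p < 0.05. For normally distributed data, "within-group differences will be evaluated using paired-sample t-tests", and the same sentence adds that "between-group analyzes will employ Analysis of Variance (ANOVA) and the Kruskal–Wallis test". It does not rank the two kinds of test, and it does not call the paired tests descriptive.

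The Hypotheses section has two layers. The lead sentence is comparative: Qigong participation "will differ significantly from aerobic and waiting exercises in terms of emotional cognition and attention". The numbered H1 is not: participation "is expected to markedly improve acupuncturists’ capabilities in emotion regulation, attention, and cognition", with no control mentioned. Objective 1 is comparative again, the effects being judged "compared to regular aerobic exercise and a control group on a waiting list".

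On design, the Participants section says "They will be randomly assigned in a 1:1:1 ratio" to Baduanjin, aerobic exercise or waiting list. Each entrant must "Be a full-time acupuncture student with completed courses" behind them. All behavioural and hand-function instruments are given one week before the intervention and at weeks 12 and 24 (Procedure; Table 1).

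**The concern.** Taken literally, H1 asks whether Baduanjin participants improve, and the listed test that answers that question is the paired t-test in the Baduanjin arm. That test measures everything that happens to those participants between visits, not only the exercise.

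Two other sources of change are plausible here. The first is retesting. The Schulte table, a primary outcome, is a performance task given three times, as are the pegboard and the needling test among the secondary outcomes. The second is continuing study: the participants are full-time students of acupuncture, and needling skill may rise in every arm over about 25 weeks.

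Randomisation with a waiting-list arm deals with both sources, but only when arms are compared directly. If a within-arm result is reported as support for H1, the claim rests on an uncontrolled before-after comparison inside a randomised trial.

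**Working it through.** **Inputs from the protocol article.** Two-sided level 0.05 (Behavioral analysis). 33 enrolled per arm with 10% dropout allowed (Sample size estimation), so 33 × 0.9 = 29.7, or about 30 completers per arm. Three arms, 1:1:1. The article states no effect size, SD, correlation or power, so it has no figure of its own to reproduce on this point.

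**Assumptions.** Change scores are normal. All three arms share the same mean change, so there is no intervention effect. The size of that change is unknown and is varied. Write d for the common mean change divided by the SD of the change score.

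**Paired test in one arm.** The statistic follows a noncentral t distribution with n − 1 = 29 degrees of freedom and noncentrality d√n. The test is significant when the absolute value of t exceeds the two-sided 5% critical value. For d = 0.3 the noncentrality is 0.3 × √30 = 1.64.

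**Between-arm test.** A one-way ANOVA on change scores, simulated 40,000 times per value of d under the same assumptions.

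| Common change d | Baduanjin paired test significant | Between-arm ANOVA on change significant |
|---|---|---|
| 0 | 5% | 4.9% |
| 0.2 | 18.5% | 5.1% |
| 0.3 | 35.5% | 4.9% |
| 0.5 | 75% | 4.8% |
| 0.8 | 99% | 5.0% |

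With all 33 per arm analysed, the paired-test figures for d = 0.2, 0.3 and 0.5 are 20%, 39% and 80%.

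**In baseline SDs.** If the gain is g baseline SDs and the correlation between visits is r, with equal SDs at both visits, then d = g / √(2(1 − r)). For g = 0.3 and r = 0.7, d = 0.3 / √0.6 = 0.387, and the paired test is significant in 54% of trials. Moving r from 0.5 to 0.8 at the same gain gives 36% to 71%.

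**Reading the table.** A shift shared by all arms cancels in the between-arm comparison, so its error rate stays at 5% whatever d is. The paired test correctly detects that something changed, but it cannot say what caused the change.

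**The case against.** The strongest reply is that the article already has the right comparison. The lead hypothesis and objective 1 are both comparative, the paired tests share their sentence with between-arm tests, and the waiting-list arm is assessed on the same schedule. Nothing assigns the paired tests to H1. The article also says that a detailed statistical plan will go to the statisticians before analysis. That plan is not shown and may settle which test decides.

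Most of this stands, and it limits the point. Three stronger readings are tempting and are not supported:

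- **That the plan lets H1 be declared met with no difference between arms.** This holds only if H1 is read apart from the sentence above it and objective 1. The text leaves the reading open but does not call for it.
- **That the plan compares which arms reach significance.** No such procedure is described. Under the assumptions above, significance in Baduanjin but not in waiting list would occur in 15%, 23% and 19% of trials at d = 0.2, 0.3 and 0.5. For two independent arms with equal rejection probability p this is p(1 − p), which cannot exceed 25%, and it falls to 1% at d = 0.8. It shows why the pattern should not be interpreted, not what the plan intends.
- **That dozens of paired tests bear on H1.** Counting 13 instruments × 3 arms × 2 follow-up visits gives 78, with 78 × 0.05 = 3.9 expected by chance. That count includes control arms and hand outcomes, which cannot support H1, and the article does not say that both follow-ups are tested against baseline. For the three primary tools in the Primary outcome measurement section, Baduanjin arm only and two visits, it is 6 tests and 6 × 0.05 = 0.3.

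It is also fair that among the primary outcomes only the Schulte table is a performance task. The others are self-report scales, for which a gain from repetition is less obvious.

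What the reply does not remove is the stated text. The article itself gives within-arm tests inferential status and itself words H1 without a control. Both are things it says, not details left to another document.

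**Conclusion.** The point holds as a defect of wording and hierarchy. The within-arm paired tests carry the same threshold as the between-arm tests but tell nothing about the trial's comparative question, and H1 drops the comparison that the lead hypothesis and objective 1 make. With no intervention effect, the chance of a significant Baduanjin paired test runs from 5% with no shared change to about 75% with a shared change of 0.5 SD of the change score, against about 5% throughout for a between-arm test of change. These figures rest on 30 completers per arm, normal change scores and an assumed common change. The documents give no value for that change, so the range matters more than any single entry.

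A reader might go further and infer that the trial will be judged on pre-post change. The comparative lead hypothesis, objective 1 and the planned between-arm tests do not support that. The sample size is not affected.

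**What to change.** 1. **Hypotheses.** Align H1 with the lead sentence and objective 1: Baduanjin is expected to improve emotion regulation, attention and cognition more than aerobic exercise and more than waiting list.
2. **Behavioral analysis.** State that H1 is decided only by the between-arm comparison of follow-up values, adjusted for the baseline values already collected, with Baduanjin contrasted against each control.
3. **Behavioral analysis.** Label within-arm changes descriptive and draw no significance claim from them. Replacing the p-values with 95% confidence intervals would not be enough: a t-based interval for an arm's mean change excludes zero exactly when the paired t-test gives p < 0.05, so the label has to be explicit.

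The cost is a few sentences in two sections and fewer significant p-values to report. Visits, instruments and enrolment stay as they are. If the unseen statistical plan already sets this hierarchy, the article need only be brought into line with it.
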